#### Infant’s state observation at discharge

The Neonatal Behavioral Assessment Scale (NBAS) was developed by [name] to examine infant behavioral capacity [70]. According to the NBAS, items are selected to assess infants’ state regulation before hospital discharge. States are defined as follows: *Quiet sleep* - deep sleep with regular breathing, eyes closed, no spontaneous activity; *Active sleep* - light sleep with eyes closed, rapid eye movements can be observed, low activity level; *Sleep-wake transition* - drowsy or semidozing, eyes may be open, dull and heavy lidded, even closed, activity level variable, reactive to sensory stimuli, but response is delayed, state change after stimulation frequently noted, movements are usually smooth, dazed look when the infant is not processing information and is not fully alert; *Unfocused wakefulness* - alert, with a bright look, the infant seems to focus attention on source of stimulation, motor activity is at a minimum, a kind of glazed look exists, which can be easily broken through; *Alert wakefulness* - eyes open, considerable motor activity with movements of the extremities, reactive to external stimulation with startles and motor activity; *Fuss/cry* - intense crying, which is difficult to break through with stimulation, motor activity is high, the typical crying face with cupped tongue should be seen.

Observations will take place during the same time period (12:30–13:30 pm) by one trained researcher. The researcher will note the predominant state expressions during the first minute of every 10-min period throughout the hour of observation.

#### Fathers’ mental status

The State-Trait Anxiety Inventory (STAI) will be used to assess fathers’ mental status in regard to state and trait anxiety [71]. The questionnaire consists of two parts, each containing 20 statements. One part assesses state anxiety, and the other part assesses trait anxiety. This questionnaire was translated into a Chinese version in 1988, and the internal consistency reliability was 0.95 [72, 73]. All items are scored according to a 4-point Likert scale. Two parts are calculated, with a minimum score of 20 and a maximum score of 80. Higher scores indicate higher levels of anxiety.

Fathers will complete this questionnaire at the following time points: (1) 1 day to 3 days after the infant’s birth and (2) when the infant is discharged from the NICU.

#### Father-infant attachment

Father-infant attachment will be evaluated by the use of the Paternal Postnatal Attachment Scale (PPAS) originally designed by John T. Condon and colleagues [74]. This is a 19-item, self-report questionnaire including three subscales: patience and tolerance, pleasure in interaction, and affection and pride. The reliability and construct validity of the instrument has been well established, with the Cronbach’s alpha ranging from 0.7–0.8 [75]. Consent for using this questionnaire was obtained from the original authors. The original PPAS has been translated into Chinese and back-translated into English, and it was revised to check for any difference between the two versions. The reliability of the Chinese version scale was 0.809.

Fathers will receive the online PPAS at 4 and 6 months after discharge from the NICU to assess the father-infant relationship.

### Adverse events

This study will be implemented under thorough assessment and close monitoring by the medical staff. Although negative effects are rare, there is a chance that infants may have hypothermia or hypoglycemia or experience physiological instability during SSC. If negative effects occur, SSC will be discontinued, and the infants will be reassessed by medical staff.

### Sample size

The sample size is calculated based on the results from Xiaomei Cong [19] on the level of salivary cortisol of study 2, KCH (kangaroo care heel stick study condition): mean (M) = 0.21, standard deviation (SD) = 0.12; IH (incubator heel stick study condition): M = 0.57, SD = 0.61. We estimate that a sample size of 25 participants per group (50 in total) would be sufficient to detect a difference between the experimental group and the control group, assuming a two-tailed test for a type I error of 5% and a type II error of 20%. This sample size is calculated using the G*Power 3.1.9.2 software. Additional file 1 details the sample size calculation.

### Recruitment

Infants admitted to the NICU ward of the Women’s Hospital School of Medicine Zhejiang University, where more than 300 LBW infants are being treated per year, are eligible. Recruitment is being conducted between September 2017 and April 2019.

### Assignment of interventions

#### Allocation

A simple random sampling method is used. Fifty numbers are generated from a list of randomization codes by a medical staff member who is not involved in the experiment. The numbers are ordered from small to large; the first 25 numbers are set to be the intervention group, and the remaining numbers are set to be the control group. Fifty numbers are mixed and then put into opaque, sealed envelopes. When a preterm infant meets the inclusion criteria, he or she is assigned to either the intervention group or the control group according to the randomly generated number by a medical staff member who is not involved in the experiment.

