### Inclusion criteria:

GA between 32^0^ and 34^6^ weeks with BW ≥ 1500 gApgar scores at 1 min and 5 min ≥ 7Vaginal or caesarean deliveryMedically stable for 24–72 h (definition of stability is based on the infant’s vital signs, with temperature ranging from 36.5 to 37.5 °C, SpO_2_ > 90%, respiratory rate < 60/min, heart rate of 100 beats/min to 180 beats/min)

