## Outcome measures

### Primary outcome measure

The primary outcome is the neurodevelopmental outcomes of preterm infants, which will be measured by salivary cortisol and PIPP during hospitalization (at the age of 10–15 days) and by INFANIB and neuroimaging at term-equivalent age (40 weeks of corrected age).

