#### Premature Infant Pain Profile

The PIPP is a pain scale originally developed to assess procedural pain in preterm neonates [64]. This profile consists of seven items, including three behavioral indicators (brow bulge, eye squeeze, and nasolabial furrow), two physiological indicators (heart rate and oxygen saturation), and two contextual indicators (GA and behavioral state). Each indicator is evaluated on a 4-point Likert-type scale. Total scores range from 0 to 21, reflecting minimal to severe pain level. The construct validity and internal consistency of the PIPP have been well established [65]. Behavioral indicators will be recorded by camera, and physiological indicators will be collected via pulse oximeter. The infants’ GA will be retrieved from the medical records.

All digital video files will be independently analyzed by two researchers after they are mixed to ensure data blindness.

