### Data analysis

The data analysis will be conducted on an intention-to-treat basis. All the study subjects will be analyzed in the groups into which they were originally randomized.

Descriptive characteristics will be analyzed using frequencies and percentages. The independent *t* test and a repeated measures analysis of covariance (RM-ANCOVA) will be used to compare differences between the two groups for continuous variables. Categorical variables will be compared using the Pearson chi-square test or Fisher’s exact test. *P* values less than 0.05 will be considered significant. Data will be analyzed using the statistical software SPSS 23.0 (IBM SPSS Statistics, IBM Corporation, Armonk, NY, USA).

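### The only stated test that fits the single-time continuous outcomes (PIPP, INFANIB, MRI volumes) is an unadjusted t test, which gives up precision that gestational age and birth weight could supply

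*Protocol article*

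**What the plan says.** All references are to the protocol article.

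- **Allocation.** "A simple random sampling method is used". Fifty numbers are ordered by size, and "the first 25 numbers are set to be the intervention group, and the remaining numbers are set to be the control group". No stratification factor is named.
- **Inclusion criteria.** Entry requires "GA between 32^0^ and 34^6^ weeks" and a birth weight of at least 1500 g, so both values are known for every infant before allocation.
- **Premature Infant Pain Profile.** The seven scored items include "two contextual indicators (GA and behavioral state"; "Total scores range from 0 to 21, reflecting minimal to severe pain level". Gestational age is taken from the medical record.
- **Primary outcome measure.** The neurodevelopmental outcome is "measured by salivary cortisol and PIPP during hospitalization (at the age of 10–15 days", together with INFANIB and neuroimaging at term-equivalent age. Cortisol is sampled before and after a heel stick. The other three are described with one assessment age each.
- **Data analysis.** An independent t "test and a repeated measures analysis of covariance (RM-ANCOVA) will be used to compare differences between the two groups for continuous variables". The section does not assign a test to each outcome, names no covariate for the RM-ANCOVA, and does not mention gestational age or birth weight.

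**The concern.** Of the two methods named for continuous variables, the repeated measures model suits the cortisol pair. A score or volume taken once has no repeated factor, so the natural reading is that PIPP, INFANIB and the MRI volumes go to the t test.

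That test makes no use of gestational age. One PIPP item is fixed by gestational age at birth and cannot respond to skin-to-skin contact. Cortisol and PIPP are also measured at a fixed postnatal age of 10–15 days, so infants born less mature are less mature when tested. If these baseline variables predict the outcome, the unadjusted comparison leaves their contribution in the error term. Planned power is only just above 80%, so there is little to spare.

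**Working it through.** **1. The plan's own figure.** Inputs from Sample size: means 0.21 and 0.57, SDs 0.12 and 0.61, two-sided alpha 0.05, power 80%.

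- Pooled SD = √[(0.12² + 0.61²)/2] = 0.4396
- d = (0.57 − 0.21)/0.4396 = 0.819
- Noncentrality at 25 per arm = 0.819 × √(25/2) = 2.895. With 48 degrees of freedom, power is 81.0%. At 24 per arm it is 79.3%.

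The stated 25 per group is reproduced.

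**2. Power with adjustment.** The document gives no correlation (rho) between gestational age and any outcome, so a range is assumed. A covariate with correlation rho shrinks the residual SD by √(1 − rho²), so the effective d is 0.819/√(1 − rho²). One covariate leaves 47 degrees of freedom.

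| rho (assumed) | Effective d | Power at 25 per arm | n per arm for 80% |
|---|---|---|---|
| t test, no covariate | 0.819 | 81.0% | 25 |
| 0.1 | 0.823 | 81.3% | 25 |
| 0.2 | 0.836 | 82.5% | 24 |
| 0.3 | 0.858 | 84.4% | 23 |
| 0.4 | 0.894 | 87.2% | 21 |
| 0.5 | 0.946 | 90.6% | 19 |

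The gain is 0.3 to 3.4 percentage points for rho 0.1 to 0.3, and 6.2 to 9.6 points for rho 0.4 to 0.5.

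**3. If the covariates are useless.** At rho = 0, two covariates leave 46 degrees of freedom and power is 80.9%, against 81.0% for the t test. The downside is about 0.1 point.

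**4. Validity of the unadjusted test.** In 40,000 simulated trials per setting, the t test rejected a true null in 5.0% (rho 0.3) and 4.9% (rho 0.5). Simulated power at d = 0.819 was 81% for the t test, against 84% (rho 0.3) and 90% (rho 0.5) for ANCOVA. This agrees with the formula.

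**5. How far chance imbalance could move one estimate.** Assume gestational age is uniform over the 21 eligible days (32+0 to 34+6), so SD = 0.865 weeks.

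- Standard error of the difference in arm means = 0.865 × √(2/25) = 0.245 weeks. The 95% range is ±1.96 × 0.245 = ±0.48 weeks, or about ±3.4 days.
- The shift in an outcome, in SD units, has a 95% range of ±1.96 × rho × √(2/25): ±0.06 at rho 0.1, ±0.17 at 0.3 and ±0.28 at 0.5.
- The direct route through the PIPP item depends on its cut-points, which the article does not give. If no cut-point falls in the entry window, the shift is 0. If one does, and it separates infants by one point with fraction p on one side, the 95% range is ±1.96 × √[p(1 − p)] × √(2/25). That is ±0.17 points for a 10:90 split and ±0.28 points for 50:50, on the 0–21 scale.

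**6. What cannot be computed.** The d of 0.819 belongs to salivary cortisol. No effect size or SD is given for PIPP, INFANIB or volumes, so the table illustrates the mechanism and does not estimate the loss on those outcomes. It also assumes equal variances, whereas the planning SDs are 0.12 and 0.61.

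**The case against.** A reader might infer that the unstratified list is a flaw, or that chance imbalance in gestational age biases the result. Neither is supported. A random 25/25 split without strata is valid, and stratifying 50 infants would be a matter of choice. The t test's standard error already allows for chance imbalance. One realised estimate can be moved by it, but the expectation and the type I error are not.

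A reader might also call gestational age a strong covariate. The document does not show this. Entry is limited to less than three weeks of gestation, which restricts what it can explain, and the PIPP item may be constant across the window. INFANIB and MRI are timed by corrected age, which already brings infants close together in maturity at testing, so the gain there may be smaller.

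The last objection is that covariates are commonly left to an analysis plan, which is not shown, and that the article does not tie tests to outcomes. RM-ANCOVA does imply some covariate. This carries weight: that single-time outcomes go to the t test is a reading, although the only one the named methods allow. But the point is not that a covariate list is absent. The article states a method for these outcomes, and a better one is available from data already held.

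**Conclusion.** The point holds as one of precision. For single-time continuous outcomes the stated method is an unadjusted t test, although two pre-randomisation variables are in hand and one of them is a component of a primary score. Validity is not in question.

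The gain from adjustment is uncertain. At the cortisol planning effect it is negligible to modest (under 4 points of power) for correlations up to 0.3, and material (6 to 10 points) only at 0.4 to 0.5. These correlations are assumptions. No figure can be given for PIPP, INFANIB or volumes. The case for changing the plan rests on the near-zero cost and on fixing the covariates before outcome data are seen, since covariates chosen after an imbalance appears are open to selection.

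**What to change.** Keep the allocation as it is. In Data analysis:

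- For PIPP, INFANIB and the MRI volumes, replace the independent t test with ANCOVA on group, gestational age at birth and birth weight.
- For cortisol, name the same two covariates in the RM-ANCOVA.
- Keep the unadjusted comparison as a sensitivity analysis.

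The cost is a change of wording and two degrees of freedom (48 to 46 for a single-time outcome). No new data are needed and recruitment is unaffected. The change should be made before outcome data are analysed.

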### Data collection, management, and analysis

#### Data collection

Two researchers will collect the data, which will be kept in a locked cabinet in the NICU. The data are accessible only by the researchers. The following clinical data will be collected: (1) parents’ and infants’ demographics, collected from the medical record; (2) infants’ condition during hospitalization: daily weight, head circumference, temperature, oxygen saturation and heart rate, total amount of enteral and parenteral nutrition given, any sepsis or infection, NEC, duration of antibiotic, biomedical, ultrasound, X-ray and any other test results, any adverse events; (3) observation of SSC: time and frequency of SSC, any cause for interruption or termination of SSC, adverse events; (4) the online STAI and PPAS questionnaires, sent to the fathers’ telephones, with the completed data collected and securely stored by the SoJump online survey software.

#### Biological specimen management

The infants’ saliva will be collected, and samples will be transferred to the laboratory. The saliva will be centrifuged at 4000 rpm for 15 min. Afterward, the samples will be safely stored at − 40 °C until analysis. A radioimmunoassay for cortisol will be used to analyze cortisol concentrations in the saliva. No additional specimens will be stored, and all samples will be discarded appropriately.

### Data analysis

The data analysis will be conducted on an intention-to-treat basis. All the study subjects will be analyzed in the groups into which they were originally randomized.

Descriptive characteristics will be analyzed using frequencies and percentages. The independent *t* test and a repeated measures analysis of covariance (RM-ANCOVA) will be used to compare differences between the two groups for continuous variables. Categorical variables will be compared using the Pearson chi-square test or Fisher’s exact test. *P* values less than 0.05 will be considered significant. Data will be analyzed using the statistical software SPSS 23.0 (IBM SPSS Statistics, IBM Corporation, Armonk, NY, USA).

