### Patient adherence

To ensure participant adherence, the investigator will maintain close contact with the fathers in the SSC group and coordinate the intervention time with fathers at their convenience. Fathers may withdraw from the trial for any reason at any time. Fathers who commit to participation but miss several sessions of SSC because of work or time limitations will be allowed.

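### RM-ANCOVA in its usual complete-case form drops anyone missing one of two measurements, which falls short of the promise to analyse all study subjects

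*Protocol article*

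**What the plan says.** The Data analysis section of the protocol article makes three statements that bear on each other.

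- Analysis set: "The data analysis will be conducted on an intention-to-treat basis", followed by "All the study subjects will be analyzed in the groups into which they were originally randomized".
- Method: with the independent t test, "a repeated measures analysis of covariance (RM-ANCOVA) will be used to compare differences between the two groups for continuous variables". The section does not say which outcome goes to which method, and it names no covariates.
- Software: "Data will be analyzed using the statistical software SPSS 23.0". No procedure within the package is named.

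Three outcomes are measured exactly twice, each described in its own section: salivary cortisol before and after a heel stick, STAI at 1 to 3 days and at discharge, and PPAS, for which "Fathers will receive the online PPAS at 4 and 6 months after discharge from the NICU". The Data collection section adds that STAI and PPAS are online questionnaires sent to the fathers' telephones. The Patient adherence section foresees loss: "Fathers may withdraw from the trial for any reason at any time". INFANIB and neuroimaging are each measured once, at term-equivalent age.

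**The concern.** The usual RM-ANCOVA works on one row per participant and needs that row to be complete. A father who answers the PPAS at 4 months but not at 6 is removed altogether, and his 4-month answer with him. An infant with one unusable saliva sample is removed in the same way.

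Two things are at stake. First, the analysis would be called intention-to-treat and described as covering all subjects, while it covers only those with complete data. Second, complete-case estimates can be biased if the chance of a missing second value depends on the first value, particularly if that dependence differs by arm. The trial has only 50 participants, so collected data should not be thrown away by choice of method. PPAS is probably the most exposed outcome, because it is self-reported online months after discharge.

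**Working it through.** **Which outcomes can be affected**

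| Outcome | Measurements | Exposed to deletion for one missing value of two? |
|---|---|---|
| Salivary cortisol | before and after heel stick | yes |
| STAI | 1 to 3 days; discharge | yes |
| PPAS | 4 and 6 months after discharge | yes |
| INFANIB, MRI | once | no |

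**The plan's own figure.** The Sample size section uses cortisol means (SD) of 0.21 (0.12) and 0.57 (0.61), two-sided 5% and 80% power.
- Pooled SD = √((0.12² + 0.61²)/2) = √0.19325 = 0.4396.
- d = (0.57 − 0.21)/0.4396 = 0.819.
- Noncentral-t power is 0.793 with 24 per group and 0.810 with 25.

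The stated 25 per group is therefore reproduced as the number needed with no loss. This figure concerns cortisol only and is not used below.

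**How many participants each approach uses.** The article gives no missing-data rate, so let m be an assumed probability of a missing value at each of two time points, independent between them.
- Complete at both: (1 − m)².
- At least one value: 1 − m².
- Exactly one value, which complete-case analysis discards: 2m(1 − m).

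| m | Complete at both | At least one value | Discarded although observed |
|---|---|---|---|
| 10% | 0.81 (40.5 of 50) | 0.99 (49.5) | 0.18 (9) |
| 15% | 0.7225 (36.1) | 0.9775 (48.9) | 0.255 (12.75) |
| 20% | 0.64 (32) | 0.96 (48) | 0.32 (16) |

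**Sensitivity to independence.** Suppose instead that every loss is a withdrawal before the first measurement, so both values are missing together. Then both approaches use 1 − m, that is 90%, 85% or 80%, and the mixed model gains nothing. Real loss probably lies between these two patterns.

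**Whether bias is possible.** An illustrative simulation assumed 25 per arm, a within-participant correlation of 0.6 and a true difference of 0.80 SD at both time points. About 16% of second values were missing, depending on the first value and in opposite directions in the two arms. The complete-case difference, averaged over both time points, had mean 1.05. A likelihood estimate using all observed values had mean 0.80. This shows that bias can arise. Its size and direction follow entirely from the assumed mechanism, and nothing in the article supports that mechanism for this trial.

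**The case against.** A reader might infer that RM-ANCOVA simply cannot deliver the promised intention-to-treat analysis. The article does not support that. It names neither the SPSS general linear model procedure nor a complete-case rule, and it does not assign RM-ANCOVA to particular outcomes. With complete data, or on multiply imputed data, the conflict disappears. Silence on missing data is also no fault in a condensed article, since the full protocol or SAP may cover it. All of this stands and makes the point conditional. What remains is that the article did choose a method, and the usual form of that method pulls against the analysis set promised beside it.

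The intention-to-treat sentence can also be read mainly as a rule on allocation: no switching of groups and no per-protocol exclusions. RM-ANCOVA respects that rule. On the stricter reading, a mixed model falls short too, because it omits anyone with no outcome value at all (1% to 4% in the table above). The t test equally omits anyone without a single-time outcome. So the mixed model comes closer to the promise without meeting it fully.

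A reader might also apply the effect size of 0.82 to PPAS and quote a loss of power. That is not supported: the effect belongs to cortisol, and the article gives no effect size or power for PPAS. For cortisol, both samples surround one heel stick, and nothing suggests loss of 10% to 20% per sample.

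Differential loss is plausible only. The Patient adherence section commits the investigator to close contact with fathers in the SSC group and states no equivalent for the control group. That commitment concerns attendance at sessions, and the article gives no questionnaire loss by arm.

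**Conclusion.** The point holds in conditional form. If any value is missing on cortisol, STAI or PPAS and nothing is imputed, RM-ANCOVA as usually run discards observed data and analyses fewer than all study subjects. It may also be biased if loss depends on earlier scores.

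Under assumed independent loss of 10% to 20% per time point, 81% to 64% of participants are kept, against 99% to 96% with at least one value. The gap narrows as more losses affect both time points, and it closes if all do. No power loss for PPAS and no direction of bias can be stated from the article. Allocation as randomised is unaffected, and INFANIB and MRI lie outside the point.

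**What to change.** In the Data analysis section, replace RM-ANCOVA with a linear mixed model for cortisol, STAI and PPAS: SPSS MIXED, restricted maximum likelihood, fixed effects for arm, time and arm-by-time, unstructured within-participant covariance, all available observations. Keep both measurements as outcomes; a first measurement entered as a covariate would again remove participants who lack it. State that participants with no value on an outcome do not contribute to its analysis, so that the wording on the analysis set matches what is done.

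The cost is a change of wording and slightly more analysis work in the software already named. The model relies on values being missing at random given the observed data, and the text should say so. Design, sample size and data collection do not change.
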